# STUDY POPULATION

# Population (base)

The maximum number of patients will be 144 (constant alpha=0.014, cumulative alpha=0.05; beta =0.10). This means that with a true failure rate of 10%, the probability of passing the upper boundary is below 5%, with a power of 90%. It is expected that the patients will be recruited within a period of 2 years in the above mentioned centers.

**Inclusion criteria**

- Low and high risk patients (according American Join Committee on Cancer, AJCC 6) with recently diagnosed histological proven DTC, who have to be treated with ablation therapy.

TNM stages T1>1cm, T2, T3, N0, N1, M0 are to be included.

- Aged 18 years or older

- Not pregnant

- No major concurrent diseases leading to a reduced survival of < 1 year

- Normal renal function (serum creatinine level < 130 µmol/l or clearance > 40 ml/min).

**Exclusion criteria**

- Stage T4

- Stage M1 when known before ablation

# Sample size calculation

See Power Analysis, page 14.

# METHODS

**Study procedures (also see flowchart)**

After total thyroidectomy and histological confirmation of differentiated thyroid cancer

substitution therapy is started (levothyroxine) to reach a TSH level < 0.3 mU/l.

- *3-6* weeks post surgery

Neck ultrasound (standard application) to confirm the absence of significant thyroid remnant and to screen for lymph nodes. Basal TSH and Tg measurement.

Additional blood sample for storage and additional blood sample for bone markers

*- 6 weeks post surgery*

0.9 mg rhTSH will be administered i.m. at 0 and 24 hours. (Monday and Tuesday)

At 48 hours 3.7 GBq (100 mCi) I-131 will be administered.

Post treatment scan 7 - 10 days after I-131 application

TSH and Tg measurement at 48 hours. Additional blood sample for bone markers

To ensure the I-deficient diet (according to the Dutch guidelines), the iodine excretion in a 24 hours urine will be measured (in µg/l,) at day 1 (Tuesday).

*- 6 months post ablation therapy*

Neck ultrasound and FNA of suspected nodules (if positive consider re-surgery).

*- 9 months post ablation therapy*

0.9 mg rhTSH will be administered i.m. at 0 and 24 hours (Monday and Tuesday).

At 48 hrs 150 MBq (4 mCi) I-131 application (Wednesday).

TSH and Tg measurement and WBS 48 hours (Friday) after administration of 150 MBq (4 mCi) I-131 (i.e. 96 hours after the first rhTSH). (In case of visible uptake on a planar view, then a SPECT view will be made if available).

Successful ablation is defined when - RhTSH Tg is < 1ng/ml and

- RhTSH dxWBS is negative* and

- Neck US is negative and

- Tg antibodies are negative

* no visible uptake in the thyroid bed or uptake < 0.1% (using a standard gamma probe) on a Dx WBS

In case one or more of the above mentioned diagnostic procedures is positive or in case of a Tg level < 1.0 ng/mL 48 hours at the time of ablation or the possibility of distant metastases, thyroid hormone withdrawal and treatment with 5550 – 7400 MBq (150-200 mCi) I-131 with post-treatment WBS is performed (standard care according to the Dutch guideline). These patients will not be removed from analysis instead the post-treatment scintigrams (as defined earlier) will be evaluated.

Successful ablation (in case of a second (blind) I131 therapy) is defined when -

- Post treatment scintigraphy is negative in the original thyroid bed

In case of a large thyroid remnant or multiple lymph nodes during ultrasound 4-6 weeks post surgery the patients will be excluded from the analysis.

All eligible patients will be treated according to the Dutch national guidelines (See addendum for treatment schedule). The only difference with the standard protocol is the period between the first and second scan. In the protocol it has been delayed to 9 instead of 6 months to eliminate the effect of Tg leakage that occurs for a long period.10, 11 There are numerous protocols and guidelines available for the treatment of thyroid cancer. Standard control after ablation therapy has been executed between 6-12 months.6 So the period of 9 months that has been chosen in this protocol is in accordance with the standard protocols that are available for thyroid cancer treatment.

*Thyroglobulin assay*

For the re-evaluations at the University Medical Centre Groningen Tg concentrations are measured using a commercial immunoradiometric assay (Brahms Tg-Plus, Heningsdorf, Germany) in a coated tube system. The Brahms Tg-Plus assay is claimed to be calibrated against the CRM 457 standard and is correlated with the former Nichols Advantage Tg assay 12 according to the following formula: Brahms assay = 0.3 x Nichols assay. In addition, the Brahms assay has an analytical sensitivity of 0.1 ng/ml and a functional sensitivity of 0.3 ng/ml (personal findings). Tg antibodies will also be measured by Brahms assay (<46 U/ml)

*Storage of body material*

It becomes clear more and more that growth factors in the blood are up regulated in the

presence of malignancy. To examine new promising tumor markers in the future, blood will be collected by vena punction with a maximum of 50 ml and stored.

Storage of material from this relatively large patient group with DTC

Is of great interest taking into account the rarity of these inherited diseases. Additionally, the current little understanding of the pathogenesis of thyroid cancer makes storage desirable, since new research may be conducted that will give more insight into the pathogenesis.

All human body material will be stored in a freezer with a temperature of -80˚C for a period of 10 years. For storage patient’s approval will be asked explicitly as a part of the informed consent. To determine whether the levels of in the future defined markers are predictors of disease activity or disease progression, clinical data will be available in order to identify important correlations. All body samples will be stored anonymously, however the study doctor is capable to trace back the patients. This is necessary in case of findings that will give additional insight in patient’s health.

*Main study parameter/endpoint*

The primary endpoint of successful ablation is defined above. Uptake will be quantified by defined methods using standard gammaprobe. The scans will be evaluated both by local and central reading:

Measurement of uptake :

A standard gammaprobe, calibrated for I-131, and similar to the one used for measuring thyroid uptake in hyperthyroidism, will be used. Measurements will be performed as described in the Dutch Recommendations for Nuclear Medicine procedures.

Central reading facility: after local reading, every 4 months post-therapy scans as obtained in the study centre will be forwarded to the central site, preferably in DICOM format to allow modification of image intensity to allow central interpretation. In case of differences in reading a consensus will be reached by the involved interpreters. Probe measurements will not be centralized.

**Withdrawal of individual subjects**

Subjects can leave the study at any time for any reason if they wish to do so without any consequences. The investigator can decide to withdraw a subject from the study for urgent medical reasons.

## Replacement of individual subjects after withdrawal

In case of individual withdrawal, statistical analysis must determine if replacement is necessary for the study results. If this is the case, other individuals will be included in the study as a new subject.

## Premature termination of the study (see Statistical Analysis, page 14)

During the study every 3 months evaluation will take place of scans and laboratory measurements. When the lower boundary is passed, sequential monitoring can be stopped, interim statistical analysis will be done and the use of rhTSH will become the standard treatment.

Final statistical analysis will be done after completion of all 144 patients.

When the upper boundary is passed, the study will be stopped prematurely and the use of rhTSH (with dosage and timing as in the protocol) can not become the standard treatment. Final statistics will be provided.

## SAFETY REPORTING

## Section 10 WMO event

In accordance to section 10, subsection 1, of the WMO, the investigator will inform the subjects and the reviewing accredited METC if anything occurs, on the basis of which it appears that the disadvantages of participation may be significantly greater than was foreseen in the research proposal. The study will be suspended pending further review by the accredited METC, except insofar as suspension would jeopardize the subjects’ health. The investigator will take care that all subjects are kept informed.

## Adverse and serious adverse events

No adverse or serious events are to be expected when using rhTSH or during scanning. In previous studies using rhTSH no adverse effects have been reported.

Adverse events are defined as any undesirable experience occurring to a subject during a clinical trial. All adverse events reported spontaneously by the subject or observed by the investiga­tor or his staff will be recorded.

A serious adverse event is any untoward medical occurrence or effect that at any dosage results in death;

- is life threatening (at the time of the event);
- requires hospitalization or prolongation of existing inpatients’ hospitalization;
- results in persistent or significant disability or incapacity;
- is a congenital anomaly or birth defect;
- is a new event of the trial likely to affect the safety of the subjects, such as an unexpected outcome of an adverse reaction, lack of efficacy of an IMP used for the treatment of a life threatening disease, major safety finding from a newly completed animal study, etc.

All SAEs will be reported to the accredited METC that approved the protocol, according to the requirements of that METC.

##

## *Follow-up of adverse events*

All AEs will be followed until they have abated, or until a stable situation has been reached. Depending on the event, follow up may require additional tests or medical procedures as indicated, and/or referral to the general physician or a medical specialist.

#

# STATISTICAL ANALYSIS

# Descriptive statistics

**Power analysis**

Data on ablation rates.

Based on literature and local Dutch data the investigators agree that a mean ablation failure rate up to 10% is considered acceptable.

Definition of ablation success : A recent review has analyzed the success rate of ablation at 80% with 100mCurie after withdrawal.7 Results from Dutch centers vary from 88% , 93% and lower (68% and 86%) and 56%.13-15

A historical ablation success rate defined on the basis of the post therapeutic scan in those patient with a second blind I131 therapy will follow.

Event = ablation failure as defined above

Event =

ablation failure as defined above

Figure 1

*Background of the sequential design with stopping rule*

A sequential design with a stopping rule equipped with two boundaries, gives the opportunity to use every single consecutive ablative therapy in a daily executed interim analysis.(see fig.1)

The preset upper boundary allows premature stopping in case of an observed failure rate that is inferior to the acceptable rate of 10%, with a rate of 20% as alternative ( Total maximal number of patients 144; constant alpha=0.014, cumulative alpha=0.05; beta =0.10). This means that with a true failure rate of 10%, the probability of passing the upper boundary is below 5%, with a power of 90%.

The preset lower boundary allows premature stopping for futile testing (constant alpha=0.2638, cumulative beta=0.10; cumulative alpha=0.05). This means that with a true failure rate of 20%, the probability of passing the lower boundary is below 10% and that the probability of subsequent passage of the upper boundary would be below 5%.

The 50% probability of stopping (because of passing the upper or lower boundary) in case of a 20% failure rate is reached within the first 50 consecutive patients, whereas the 50% probability of stopping in case of a 10% failure rate is reached within 77 patients.

During the study, there is an analysis after entering each new patient. When the lower boundary is passed, sequential monitoring can be stopped, interim statistical analysis will be done and the use of rhTSH will become the standard treatment. Final statistical analysis will be done after completion of all 144 patients.

When the upper boundary is passed, the study will be stopped prematurely and the use of rhTSH (with dosage and timing as in the protocol) can not become the standard treatment. Final statistics will be provided. Then two alternatives can be followed: withdrawal remains the standard treatment or a new study is started with different time and/or dosing of rhTSH.

The probabilities of stopping with various true failure rates are given in figure 2.

Figure 2 Probability of stopping at different failure rates 5 -25%

*Stopping rule with two boundaries*

*The upper boundary*

For one group of patients we can investigate inferiority of the failure rate p to H0: p<=p0 with the alternative H1:p>=p1. With a fully sequential design an upper boundary UB(n) can be constructed, being the maximally accepted number of events within n consecutive patients.

If the failure rate is p, then P(p,n-1,UB(n-1)) is the probability that the number of failures after (n-1) patients is UB(n-1). When the chosen one-sided level of significance is alpha(n-1), then P(p,n-1,Ub(n-1))>= alpha(n-1). Also alpha(n) has been chosen. In case an event occurs in patient n, there are two possibilities:

1) (P(p,n-1,UB(n-1)))*p=P(p,n,UB(n-1)+1)<alpha(n). This would mean that this result

is unacceptable, activating the stopping rule. Thus the upper boundary has been

passed, making UB(n-1)=UB(n). The probability of passage is P(p,n,UB(n)+1).

2) (P(p,n-1,UB(n-1)))*p=P(p,n,UB(n-1)+1)>=alpha(n). This would mean that this

result is acceptable, leaving the stopping rule inactivated. The upper boundary is

not passed, making UB(n)=UB(n-1)+1. The probability of passage is

P(p,n,UB(n)+1)=0.

The cumulative probability P(sum UB) to pass the upper boundary is the sum of P(p,n,UB(n)+1) from n=1 to n=N. N is the maximum of patients needed.

For p=p0 P(p0,sum UB) should not exceed a chosen value of alpha(rule). And for p=p1 P(p1,sum UB) should exceed a chosen value of (1-beta(rule)), being the power.

In this way the upper boundary serves as a fully sequential test of inferiority. When the boundary is passed, we do not accept H0 and declare the failure rate inferior to p0.

*The value of alpha(n).*

1. With alpha(n) declining with rising n, as with the method of Pocock 16, the probability of "discordant" activation of the stopping rule is larger than with a constant alpha(n).17 Following the method of O'Brien en Fleming with a constant alpha(n)18, one would expect alpha(n)=alpha(rule)/N. This is not the case, because UB(n) is discrete in nature. Alpha(n) is larger than alpha(rule)/N. Z(1-alpha(n)) approximates Z(1-alpha(rule) +CTC. CTC is the socalled Christmas tree correction, which is approximatedly 0.583 in size.19

*The calculation of UB(n)*

Conventionally, UB(n) approximates n*p0+Z(1-alpha(n))*(n*p0)^0.5. Because of the discrete character of UB(n) this transforms into:

UB(n) = integer{n*p0 +Z(1-alpha(n)) *(n*p0)^0.5 +1}.

*The value of N*

The value of N can now be calculated as

N= integer{[Z(1-alpha(n)) *(p0)^0.5+Z(1-beta(N))*(p1)^0.5/(p1-p0)]^2+1}.

*The lower boundary*

*Futile testing*.

In a sequential design a stopping rule can be equipped with a lower boundary LB(n). Passage of that boundary would mean futile testing and monitoring could be stopped, accepting H0.

When constructed in such a way that UB(N)=LB(N), we know that the probability to pass the lower boundary would be 1-alpha(rule) in case p=p0 and (1-beta(rule)) in case p=p1, because of the limits set for UB(n).

Suppose the number of events after (n-1) patients equals LB(n-1) and LB(n)=LB(n-1)+1. If the failure rate is p1 and no events occur in patient n, then P(p1,n,LB(n))-1 is the probability that the number of failures after n patients is just 1 below LB(n). The overall probability to subsequently pass the upper boundary within the next (N-n) patients would be P(futile,n). P(futile,n)=0 in case LB(n)=LB(n-1). The sum P(p1, sum LB) of these probabilities P(futile,n) summed from n=1 to n=N we call alpha(futile). Alpha(futile) must be smaller than beta(rule).

Such a lower boundary can be approximated by:

LB(n)= integer{UB(N)+1-p1*(N-n)-Z(1-alpha1(n))*(p1*(N-n))^0.5)>=0. We choose alpha1(n) to be constant and with such a value that alpha(futile) is the result.

*Simultaneously active boundaries.*

The boundaries given above are still approximations. With low values of p0 and p1 the approximations do deviate from exact calculations. For this reason alone all probabilities should be calculated exactly. But there is a second reason to do so: the probability to pass one boundary is influenced by the probability to pass the other one.

Such exact calculation can be done in a spread sheet programme. The calculations are repeated with changing values of the Z-parameters until the values of alpha(rule), (1-beta(rule)) and alpha(futile) meet the limits set.

Estimation of the failure rate p after activation of the stopping rule.

If a boundary is passed after k patients, with a total number of events of (UB(n)+1) for the upper boundary or of( LB(n)-1) for the lower boundary, p can be estimated.

When the true failure rate is p, then

a) After passing the upper boundary: the sum of (P(p,n,UB(n)+1) from n=1 to n=k is

0.5 for the estimation of p, whereas this sum is alpha(rule) for the upper limit of its

100*(1- 2*alpha(rule)) % confidence interval (CI) and 0.95 for the lower limit of this

CI.

b) After passing the lower boundary: the sum of (P(p,n,LB(n)-1) from n=1 to n=k is

0.5 for the estimation of p, whereas this sum is alpha(rule) for the lower limit of its

100*(1- 2*alpha(rule)) % confidence interval (CI) and 0.95 for the upper limit of this

CI.

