# STUDY DESIGN

Multicenter study in the Netherlands.

A conventional design would be to perform a randomized study comparing TSH preparation with endogenous TSH rise. However, the disadvantage of a randomized study is the tremendous number of patients needed, which is calculated to be 552 patients (based on an acceptable ablation failure rate of 10% versus an alternative hypothesis of 20%, power 90%, alpha 0.05). In addition, even after having performed a randomized study, the main question remains whether the ablation failure rates in the rhTSH arm would be acceptable for widespread application. For example, a statistically higher failure rate after rhTSH could still be considered clinically acceptable.

Therefore, to confirm that the efficacy of rhTSH pre-treatment for ablation therapy is not inferior to withdrawal of thyroid hormone, a fully sequential design will be used, with preset boundaries for stopping in case of inferiority or equality of the rhTSH strategy.

If the failure score by rhTSH passes the upper boundary of the acceptable failure rate then rhTSH is considered inferior to the conventional withdrawal ablation. If failure score after rhTSH passes the lower boundary than rhTSH stimulation is at least equal. This design is less conventional, but is expected to grow significantly in medical research as it provides very clear answers, without the need to confirm what is already known over and over (as is the case in the standard arm of a RCT). 9 (See also statistical analysis)

This is a prospective observational study and a fully sequential design will be used, with preset boundaries for stopping in case of inferiority or equality of the rhTSH strategy.

All patients will be treated according protocol using rhTSH (Dutch guidelines). All scan and laboratory evaluation together the treatment decision will be executed in the participating centers. Scans and blood for central reading will be collected and re-evaluated in Groningen every 4 months. This re-evaluation is the study evaluation and will not change the standard treatment.

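### Analysing after each patient's entry is impossible with a 9-month endpoint, and the 50- and 77-patient stopping figures count evaluated patients, not patients already treated

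*Protocol*

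**What the plan says.** The Power analysis section of the protocol describes a fully sequential rule with an upper and a lower boundary, intended to "use every single consecutive ablative therapy in a daily executed interim analysis". It then states: "During the study, there is an analysis after entering each new patient". Its design constants are "Total maximal number of patients 144; constant alpha=0.014, cumulative alpha=0.05; beta =0.10" for the upper boundary and "constant alpha=0.2638, cumulative beta=0.10; cumulative alpha=0.05" for the lower, testing an "acceptable rate of 10%, with a rate of 20% as alternative". It puts the 50% probability of stopping at 50 patients if the true failure rate is 20%, and at 77 patients if it is 10%.

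Other sections give a different timetable. Premature termination of the study says: "During the study every 3 months evaluation will take place of scans and laboratory measurements". Study Design says: "Scans and blood for central reading will be collected and re-evaluated in Groningen every 4 months", and calls that re-evaluation the study evaluation. The endpoint text under Methods repeats the 4-month interval.

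Under Study procedures the endpoint is assessed 9 months after ablation. Patients with a positive finding go on to thyroid hormone withdrawal and a second I-131 treatment, stay in the analysis, and are classified on the scan after that treatment. On accrual, Population (base) says: "It is expected that the patients will be recruited within a period of 2 years".

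Only crossing the upper boundary stops the study. After a lower crossing, sequential monitoring can stop, but the final analysis waits for all 144 patients.

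**The concern.** A patient's entry adds no information to a chart of 9-month outcomes, so the rule cannot be run as written. The quarterly and four-monthly timetables cannot both be the schedule on which the boundaries are checked.

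Three things follow.

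- **Overrun.** Patients keep being ablated while outcomes are awaited. The stopping figures do not count them, and the estimation method at the end of the Statistical Analysis section uses only the k patients evaluated at the crossing. Nothing says how the outstanding outcomes are used after an upper crossing.
- **Batching.** It is not stated whether a batch of results is tested one patient at a time or only at its end.
- **Outcome-dependent delay.** A clear success is final at 9 months. A potential failure becomes final only after a second treatment and scan. If results are charted as they become final, successes enter first and the chart drifts towards the lower boundary, where rhTSH would be adopted as standard treatment.

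**Working it through.** **Inputs.** From the protocol: N = 144, p0 = 0.10, p1 = 0.20, per-look alpha 0.014 (Z = 2.197), lower-boundary alpha 0.2638 (Z = 0.632), outcome at 9 months, recruitment over 2 years, reading every 3 or 4 months. Assumption: uniform accrual.

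**1. Reproducing the plan's figures.**
- UB(n) = integer{n·p0 + Z·√(n·p0) + 1}. UB(144) = integer{14.4 + 2.197 × √14.4 + 1} = integer{23.7} = 23.
- LB(n) = integer{UB(N) + 1 − p1(N−n) − Z·√(p1(N−n))}, not below 0. LB(144) = 24.
- An exact patient-by-patient recursion with both boundaries active gives upper crossing at a true 10% of 0.0508 with 0.014 taken exactly (0.0498 with 0.0139, which rounds to 0.014). At a true 20%, power is 0.899 and lower crossing 0.101. Median stopping is at 50 patients (true 20%) and 76 (true 10%).
- These agree with the stated 5%, 90%, 50 and 77 to within rounding. They assume that each outcome is known at once.

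**2. Patients ablated when outcome k is known.** Accrual is 144/24 = 6 per month, so 6 × 9 = 54 are ablated during one endpoint wait. The number ablated is min(144, k + rate × (9 + reading lag)).

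| Case | k = 50 | k = 77 |
|---|---|---|
| No reading lag | 50 + 54 = 104 | 77 + 54 = 131 |
| Average lag, 1.5–2 months | 113–116 | 140–143 |
| Full lag, 3 months | 122 | 144 (cap) |
| Full lag, 4 months | 128 | 144 (cap) |
| Accrual over 36 months (4 per month), lag 0–4 months | 86–102 | 113–129 |

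Averaged over upper crossings at a true 20%, 51 patients would have been ablated with immediate outcomes, about 102 with a 9-month delay and 120 with a 13-month delay.

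**3. Testing only at batch ends.** Three months yields 18 outcomes and four months 24.

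| Looks | Upper crossing at 10% | Power at 20% | Lower crossing at 20% |
|---|---|---|---|
| Each patient, in order | 0.051 | 0.899 | 0.101 |
| Every 18 outcomes | 0.026 | 0.883 | 0.117 |
| Every 24 outcomes | 0.024 | 0.887 | 0.113 |

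Shifting the phase of the looks gives alpha of 0.020–0.032 and power of 0.880–0.894. If results from a batch are charted one by one in ablation order, the first row applies unchanged.

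**4. Charting in order of result arrival.** Assumptions, not in the protocol: 35% of patients need a second treatment, 20% truly fail (all within that 35%), and the extra delay is 2–4 months. By simulation, the probability of crossing the lower boundary at a true 20% is about 10% with no extra delay. It rises to about 17–29% if each result is charted when final, and to about 12–22% if results are released in 3- or 4-month batches. The proportion needing a second treatment matters: without batching, 25% gives about 19–32% and 50% gives about 16–22%.

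**The case against.** A reader might infer that the stated error rates fail under the planned monitoring. The document does not support that. The boundaries are defined on consecutive patients, most naturally read as ablation order, and in that order alpha and power are unchanged however results are batched. Testing only at batch ends makes the rule conservative: alpha falls to 0.02–0.03, and the cost is one to two points of power. No passage prescribes arrival-order charting, and the 35% and the 2–4 months behind its figures are assumptions. This objection stands. The remaining point is that ablation order and waiting for pending patients are implied at most, never stated.

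The figures at k = 77 carry less weight than they seem to. At a true 10%, about 95% of stops are at the lower boundary, after which the protocol intends to complete all 144 patients anyway. That also stands.

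It would also be wrong to say that early stopping is the reason for the design. Study Design gives the reasons as avoiding a 552-patient randomised trial and asking whether the rhTSH failure rate is acceptable, and a maximum of 144 delivers that saving even with full overrun. Nor are patients exposed to something otherwise unavailable, since the Introduction says the Dutch guidelines already permit rhTSH.

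Finally, the daily analysis appears in a background sentence and describes the same fully sequential method as analysis after each patient. The real conflict is between three timetables: per patient, 3-monthly and 4-monthly.

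**Conclusion.** The point holds as a defect in the monitoring rule and in the stopping figures, not as a failure of the error rates. Analysis at each patient's entry cannot be done with this endpoint, and the three timetables must be reconciled.

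Under uniform accrual over 24 months, the 50-patient stopping point corresponds to about 104 patients ablated, up to 122–128 with a full reading lag, or 86–102 if accrual takes 36 months. This bites at the upper boundary, where the study stops and the use of outstanding outcomes is undefined.

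The planned alpha and power hold if the boundaries are applied patient by patient in ablation order and wait for pending second-treatment patients. Batch-end looks alone cost little: power of about 88–89% and acceptance at a true 20% of 11–12%, against the stated 90% and below 10%. The larger risk, acceptance at a true 20% of about 12–22% with batching or 17–29% without, depends on arrival-order charting and the assumptions in step 4. It is a route that the wording leaves open, not one that it prescribes.

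**What to change.** - State one monitoring calendar in Study Design, Premature termination and Power analysis, and remove the analysis at entry of each patient.
- Say that within each batch UB(n) and LB(n) are applied patient by patient in order of ablation date, only up to the first patient not finally classified.
- Say that after an upper crossing all patients already ablated are followed to classification, and that the failure-rate estimate is reported with and without them.
- Beside the 50- and 77-patient figures, give the expected number ablated at stopping, with the accrual and reading-lag assumptions.

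The cost is protocol wording. Looks will sometimes wait for patients whose second-treatment scan is pending, and the early-stopping figures will look less favourable. The sample size and the boundaries do not change.

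### The written stopping criterion uses alpha(n)=0.014 as a point probability and the boundary formula uses it as a tail area; the two give different upper boundaries, and only the formula fits the stated 5% and 90%.

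*Protocol*

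**What the plan says.** All of this is in the Protocol, Statistical Analysis, *Power analysis* and its subsections.

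- **Design values.** The investigators hold that "a mean ablation failure rate up to 10% is considered acceptable", "with a rate of 20% as alternative". The constants are "Total maximal number of patients 144; constant alpha=0.014, cumulative alpha=0.05; beta =0.10", and the lower boundary has its own constant of 0.2638. The stated properties are below 5% upper passage at a 10% failure rate, 90% power at 20%, below 10% lower passage at 20%, and a 50% chance of having stopped by 77 patients (at 10%) and 50 patients (at 20%).
- **Criterion under *The upper boundary*.** P(p,n-1,UB(n-1)) is defined as the probability that the failure count equals the boundary. If the next patient fails, the rule is activated when "P(p,n-1,UB(n-1)))*p=P(p,n,UB(n-1)+1)<alpha(n). This would mean that this result" is not acceptable; otherwise UB rises by one. The crossing probabilities, summed at p0, must not exceed alpha(rule).
- **Formula under *The calculation of UB(n)*.** "UB(n) = integer{n*p0 +Z(1-alpha(n)) *(n*p0)^0.5 +1"}. Here alpha(n) enters through a normal quantile.
- **Lower boundary.** With UB(N)=LB(N), "the probability to pass the lower boundary would be 1-alpha(rule) in case p=p0 and (1-beta(rule)) in case p=p1".
- **Maximum number of patients.** "N= integer{[Z(1-alpha(n)) *(p0)^0.5+Z(1-beta(N))*(p1)^0.5/(p1-p0)]^2+1"}.

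**The concern.** One symbol with one stated value stands for two different quantities. In the criterion, alpha(n) is compared with the probability of crossing at a single patient. In the formula it is a one-sided tail level. A per-patient crossing probability is far smaller than a tail area, so a cut-off of 0.014 on the first is a much tighter boundary than 0.014 on the second.

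The upper boundary carries the primary decision. It is to be applied after each patient, and passing it ends the study and means that rhTSH as given here cannot become standard. Whoever programs the monitoring needs one definition, and the text offers two that disagree by several failures at most sample sizes.

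**Working it through.** **Inputs.** p0=0.10, p1=0.20, N=144, alpha(n)=0.014, alpha1(n)=0.2638, alpha(rule)=0.05 and beta=0.10, all from *Power analysis*. Z(1-0.014)=2.197. All probabilities come from an exact patient-by-patient binomial recursion that removes trials as they pass a boundary.

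**1. The plan's own figures, from the formulas.**

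- UB(50): 5 + 2.197×√5 + 1 = 10.9, so 10.
- UB(144): 14.4 + 2.197×√14.4 + 1 = 23.7, so 23.

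With LB(n) from its formula and both boundaries active:

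| Property | Stated | Recomputed |
|---|---|---|
| Upper passage at 10% | below 5% | 5.08% |
| Power at 20% | 90% | 89.9% |
| Lower passage at 20% | below 10% | 10.1% |
| Median stop at 10% | 77 | 76 |
| Median stop at 20% | 50 | 50 |

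Values of alpha(n) from 0.0135 to 0.0139 also round to 0.014 and give 4.97–4.98% with about 90% power. The stated design is essentially reproduced.

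**2. The criterion as written, at 0.014 and p=0.10, starting from UB(0)=0.**

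- n=1: 0.10 is not below 0.014, so UB(1)=1.
- n=2: 0.10×0.10 = 0.010 is below 0.014. Two failures in two patients stop the trial, and UB(2)=1.
- n=3: (2×0.10×0.90)×0.10 = 0.018 is not below 0.014, so UB(3)=2.
- n=4: 0.018×0.10 = 0.0018 is below 0.014, so UB(4)=2; and so on.

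| n | UB(n), written criterion | UB(n), formula |
|---|---|---|
| 20 | 4 | 6 |
| 50 | 6 | 10 |
| 100 | 7 | 17 |
| 144 | 7 | 23 |

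Cumulative upper passage at p=0.10 under the written criterion is 10% by n=20, 32% by n=50 and 98.0% by n=144. It is also 98.0% with a lower boundary built from this rule's own UB(N)=7. With the formula's lower boundary it is about 54%. Each figure exceeds the 5% limit that the same subsection sets.

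**3. Which meaning 0.014 has.** Under the formula boundary the largest crossing probability at any one patient, at p=0.10, is 0.003, so 0.014 cannot be a per-patient crossing level for that boundary. The Protocol's link to the cumulative level, Z(0.95)+0.583 = 1.645+0.583 = 2.228, corresponds to a tail area of about 0.013. So 0.014 is a tail area.

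**4. The beta slip.** Upper passage at p1 is required to exceed 1-beta(rule), i.e. 90%. If lower passage at p1 were also 1-beta(rule), the two would sum to more than 100%, although a trial passes only one boundary first. The background paragraph says below 10%, and the recursion gives 10.1%. The intended term is beta(rule).

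**5. The expression for N.**

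- As bracketed, with beta(N)=0.10 (Z=1.2816): (2.197×0.3162 + 1.2816×0.4472/0.1)² + 1 = (0.695+5.731)² + 1 = 42.3, so 42.
- With the whole sum divided by p1-p0: ((0.695+0.573)/0.1)² + 1 = 161.8, so 161.
- The same with beta(N)=0.130 (Z=1.126): ((0.695+0.504)/0.1)² + 1 = 144.7, so 144.

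The Protocol gives beta(N) no value.

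**The case against.** The best defence is that the document contains its own check. The summed crossing probability at p0 must stay within alpha(rule), and the exact calculation is repeated, varying the Z-parameters, until all limits are met. A spreadsheet showing 98% would fail that test. The reference to Z-parameters also suggests that the boundaries came from the formulas, and Figure 1, not available here, may already plot them.

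Most of this stands. It makes it unlikely that a boundary built from the criterion would be adopted unnoticed. It does not remove the contradiction: the written criterion contains no Z-parameter to vary, the constant is stated as 0.014, and no sentence says which definition governs.

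Three stronger readings are tempting, and the documents support none of them.

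- *The design has a 98% type I error.* It does not. The formulas give the stated properties, and the 5.08% at exactly 0.014 is within the rounding of that constant.
- *The criterion stops 98% of acceptable trials whatever the lower boundary.* With the formula's lower boundary the figure is about 54%.
- *N should be 161 and not 144.* That assumes beta(N)=beta(rule)=0.10. The Protocol separates per-look from cumulative values for alpha and leaves beta(N) undefined; about 0.130 returns 144. The single-look probability of at most 23 failures in 144 patients at 20% is 0.134, which is close. Only the misplaced bracket is established.

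**Conclusion.** The concern holds as an error in the written rule. At alpha(n)=0.014 the point-probability criterion and the tail-area formula define different upper boundaries (6 against 10 failures at n=50, 7 against 23 at n=144). The criterion breaches the Protocol's 5% limit by a factor of more than ten under either lower boundary examined. The stated 5%, 90% and N=144 are not overturned.

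The criterion's figures rest on reading P as a first-passage probability. The printed equality between P(p,n-1,UB(n-1)) times p and P(p,n,UB(n-1)+1) requires that reading. The (1-beta(rule)) term at p=p1 is wrong by the Protocol's own background paragraph. The bracket in the N expression is misplaced, and N cannot be checked further without beta(N).

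**What to change.** 1. State that 0.014 and 0.2638 are the tail areas that enter the UB(n) and LB(n) formulas.
2. Delete the comparison of the point probability with alpha(n). Lowering the cut-off is not an equivalent repair: about 0.0008 brings upper passage at 10% to 4.7%, but gives UB(144)=22 and 93.9% power for the upper boundary alone, against 23 and 91.6% from the formula.
3. Change (1-beta(rule)) to beta(rule) for lower passage at p=p1.
4. Correct the bracket in the N expression, and either state the beta(N) used or say that 144 comes from the exact calculation.
5. Make the UB(n) and LB(n) values from the exact calculation, n=1 to 144, the binding rule. If Figure 1 already shows them, tabulate the same values.

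The cost is one corrected page and a table. Sample size, error rates and conduct need no redesign.
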